### Interventions

2.5

Regardless of the group allocation, patients will start the intervention one week after the baseline evaluation.

#### Control group (CG)

2.5.1

Participants from the CG will receive a single in-person education session delivered by a physiotherapist and a nutritionist. The contents of the sessions will be about lifestyle changes regarding nutrition and daily physical activity, abstinence from addictive behaviors, personal hygiene care, and hospital routines. Participants will be encouraged to bring their caregiver or a family member. At the end, participants will be offered a booklet containing all the educational information.

#### Inspiratory Muscle Training Group (IMT-G)

2.5.2

Participants from the IMT-G will receive the same treatment as the CG, plus 2 weeks of inspiratory muscle training (IMT). The IMT will be 5 days/week, lasting ∼20 min per session, using the POWERBreathe® KH2 device (Warwickshire, England, UK). The sessions will consist of 5 min of stretching exercises followed by IMT. In the first week, the intensity will be set at 50% of the maximal inspiratory pressure (MIP), with eight inspirations per minute. In the second week, there will be an increase of 10% in MIP, with eight inspirations per minute. Patients will be instructed to exercise from residual volume to maximally tolerable inspiratory volume against the inspiratory resistance. Training will be performed seated, wearing a nose clip [18].

#### Expiratory Muscle Training Group (EMT-G)

2.5.3

Participants from the EMT-G will receive the same treatment as the CG, plus 2 weeks of expiratory muscle training (EMT), 5 days/week, lasting ∼30 min per session. Sessions will start with 5 min of stretching exercises, followed by ∼8 min of specific EMT using the Philips Respironics Threshold PEP® device (Pennsylvania, USA) and conclude with abdominal resistance exercises: curl-ups, curls-ups with trunk rotation and reverse crunch (1st week: 3 exercises, four sets of 8 repetitions; 2nd week: 3 exercises, four sets of 10 repetitions). Patients will be instructed to exercise from total lung capacity until maximal tolerable expiratory volume against the expiratory resistance to the nearby residual volume. Training will be performed seated, wearing a nose clip [18]. The load will be 20 cmH2O, with 6 expirations per minute throughout the intervention.

#### Global Exercise Training Group (GET-G)

2.5.4

Participants from the GET-G will receive the same treatment as the CG plus 2 weeks of physical exercise, three sessions per week, 45-60 min per session, according to guidelines provided by the American College of Sports Medicine [19]. The GET sessions will include a warm-up, main workout, and cooldown. The warm-up and cool-down will last ∼5 min each and will encompass whole-body stretching exercises, holding the point of feeling light discomfort for 15 s. The main workout will have an aerobic and a resistance component. Aerobic: In the first week, participants will walk for 20 min on a treadmill at 70% of the mean speed achieved on the 6-min walk test and be limited by 80% of the maximum theoretical heart rate. In the second week, the intensity will increase to 80% of the mean speed achieved on the 6-min walk test but will still be limited by 80% of the maximum theoretical heart rate. Resistance: Resistance training using body weight and elastic bands will consist of 8 exercises (squats, wall chest press, calf raises, low-row, biceps plus shoulder press, curl-up, curl-up, curl-up with trunk rotation and reverse crunch). In week 1, participants will perform two sets of 8-10 repetitions, progressing to two sets of 10-12 repetitions in week 2.

Patients in exercise groups will be continuously monitored by an oximeter and self-perceived effort scale (0-10). Exercise sessions for all groups will be conducted and supervised by a physiotherapist at ULS São João.

### Evaluation moments

2.6

Patients will be evaluated at baseline, after completing the prehabilitation program (post-intervention assessment), and 30 days post-discharge (follow-up assessment) (Fig. 1). In each one of the assessments, 2 days of evaluation will be needed to complete all the procedures.

**Fig. 1 fig1:**
[figure not shown]
Study design and timeline Flowchart of study procedures. IMT: Inspiratory Muscle Training; EMT: Expiratory Muscle Training; GET: Global Exercise Training Group.

In brief, on the first day of assessments, a physician will screen for eligibility criteria and forward the eligible patients to a physiotherapist and a nutritionist, who will collect data on anthropometry, body composition, sociodemographic, clinical history, and behavioral risk factors. Thereafter, questionnaires regarding PROMs will be applied in the form of interviews. Finally, patients will be provided with an accelerometer to measure daily physical activity during waking hours until the completion of the prehabilitation program.

Patients will be evaluated for pulmonary function, respiratory muscle function, functional capacity, and physical fitness on the second assessment day.

Afterward, all patients will receive an education class and written information regarding healthy habits to follow before, during, and after hospital discharge, and those from the IMT-G, EMT-G, and GET-G will start their 2-week prehabilitation interventions at ULS São João. The study design and timeline are presented in Fig. 1.

After the prehabilitation programs, all patients will be reassessed using the same baseline procedures and then undergo the surgery. The surgical team will register information on ASA classification, ARISCAT score, minimum oxygen saturation, surgical approach, total surgical time, and extent of resection. After surgery, all patients will receive standard care, including daily medical assessment, physiotherapy care, and analgesic protocol.

PPC and other complications and LOS will be documented based on the patient's medical record. Any postoperative complications and hospital readmissions within the following 30 days will also be monitored and recorded.

After hospital discharge, patients will be referred to outpatient physiotherapy and nursing care. Three weeks post-discharge, patients will attend a medical appointment and will be scheduled for the follow-up assessment. Participants will receive an accelerometer to wear for one week. Upon completion of data collection, a cost-effectiveness analysis will be conducted to determine the actual economic cost-benefit of each protocol.

### Attendance

2.7

Attendance will be defined as the percentage of sessions attended by the patient (recorded by the physiotherapists) divided by the total number of sessions (GET-G: 6 sessions, IMT-G and EMT-G: 10 sessions).

### Adverse events and risks

2.8

The occurrence and causes of adverse events will be monitored, recorded, and reported separately for each study group.

### Outcomes

2.9

The following subsections delineate all the outcomes (summarized in Table 1) and explain how the researchers will measure them.

**Table 1 tbl1:** Outcomes instruments and time points of data collection.

Outcomes	Instruments	Time Points		
Primary Outcomes		Baseline	Post-intervention	Follow up
Postoperative pulmonary complications (PPC)	occurrence of postoperative pulmonary complications from surgery to 30 days after discharge according to the ESTS and STS (Fernandez et al., 2015).			x
Length of hospital stay (LOS)	number of days of postoperative hospitalization including hospital readmissions related to surgery, assessed in clinical data.			x
**Secondary Outcomes**		Baseline	Post-intervention	Follow up
Pulmonary function	informations captured using the equipment Quark PFT®, Cosmed (Rome, Italy).	x	x	x
Respiratory muscle function				
Aerobic endurance	6-min walk test (6-MWT), according to the American Thoracic Society (ATS) guidelines (2002).	x	x	x
Lower body strength	sit-to-stand test of the Senior Fitness Test (JONES, RIKLI & BEAM, 1999).	x	x	x
Handgrip strength	dynamometer Jamar Plus + Digital hand dynamometer (Sammons Preston Inc., Bolingbrook, Illinois, USA).	x	x	x
Balance	balance test, speed walk test (4 m) and stand-up and sit-down test (5 times) from the Short Physical Performance Battery (SPPB) (GURALNIK et al., 1994).	x	x	x
Speed walk				
Lower body power				
agility, coordination and dynamic balance	time up and go test (TUG) (Podsiadlo et al., 1991).	x	x	x
Dyspnea	modified Medical Research Council (mMRC) Dyspnea Questionnaire (RIBEIRO et al., 2022).	x	x	x
Fatigue	Fatigue Assessment Scale (FAS) (MICHIELSEN et al., 2004).	x	x	x
Anxiety and depression	Hospital Anxiety and Depression Scale (HADS) (PAIS-RIBEIRO et al., 2007).	x	x	x
Quality of life	EuroQol 5D-5L (FENG et al., 2021).	x	x	x
subjective daily physical activity	Physical Activity Questionnaire - Short Form (IPAQ-SF) (CRAIG et al., 2003).	x	x	x
objectively daily physical activity	GT3X + accelerometers (ActiGraph®, LLC, Pensacola, FL, USA).	x	x	x
Economic impact	Specific costs attributed to each intervention and comparison cost-effectiveness of each program.			x
**Other Outcomes**		Baseline	Post-intervention	Follow up
Sociodemographic variables	Interview.	x		
Medical history				
Barriers for prehabilitation program	Barriers questionnaire for prehabilitation (adapted from GHISI et al., 2012).	x		
Body Composition	bioimpedance (InBody 770®, InBody Co. Ltd., Seoul, South Korea).	x	x	x
Body mass index	Scale InBody 770 ®, InBody Co. Ltd., Seoul, South Korea)	x	x	x
tabaco smoking habits	Calculated by formula pack-years (BERNAARDS et al., 2001).	x	x	x
Food intake	1-day food record.	x	x	x

Post-intervention assessments (after finishing 2 weeks of intervention) and follow-up assessments (after 30 days of hospital discharge).

### Primary outcomes

2.10

PPC (from surgery to 30 days after discharge) will be screened according to the joint agreement and standardized definitions provided by the European Society of Thoracic Surgery (ESTS) and the Society of Thoracic Surgeons (STS) [20].

LOS and readmissions (from surgery to 30 days after discharge) will be based on the number of postoperative hospitalization days, including hospital readmissions related to surgery, assessed in clinical data. For those patients with persistent air leak, allowed to return home with a drainage tube, it be resisted the number of days util remove the tube.

### Secondary outcomes

2.11

Except for the economic cost-effectiveness analysis, all secondary outcomes will be assessed at baseline, post-intervention (before surgery), and follow-up (30 days after hospital discharge).

#### Pulmonary and respiratory muscle function

2.11.1

Pulmonary function will be assessed through absolute and relative values of forced vital capacity (L) and (%); forced expiratory volume in 1 s (L) and (%); peak expiratory flow (L/s) and (%); Tiffeneau Index (%); total lung capacity (L) and (%); diffusion lung capacity for carbon monoxide (mmol/min/kPa) and (%); diffusion lung capacity for carbon monoxide per unit alveolar volume (mmol/min/kPa/L) and (%) [21].

Respiratory muscle function will be measured through absolute and relative values of maximal voluntary ventilation (L/min) and (%); maximal inspiratory pressure (cmH2O) and (%); maximal expiratory pressure (cmH2O) and (%) [22].

This information will be captured using the equipment Quark PFT®, Cosmed (Rome, Italy).

#### Functional capacity and physical fitness

2.11.2

Functional capacity and physical fitness will be evaluated through changes in aerobic endurance, lower body strength, handgrip strength, balance, speed walk, lower body power, agility, coordination, and dynamic balance, as described below.

Aerobic endurance will be assessed by the 6-min walk test (6-MWT), according to the American Thoracic Society (ATS) guidelines [23]. Distance (in meters), maximum and minimum oxygen saturation (%), and maximum and minimum heart rate (bpm) will be recorded. Both oxygen saturation and heart rate will be collected using the Spirodoc® (Rome, Italy).

Lower body strength changes will be measured using the sit-to-stand test of the Senior Fitness Test [24]. Handgrip strength will be assessed using the dynamometer Jamar Plus + Digital hand dynamometer (Sammons Preston Inc., Bolingbrook, Illinois, USA). Measurements will be carried out according to the American Society of Hand Therapists’ Recommendations [25].

The Short Physical Performance Battery (SPPB) will be used to assess balance, walking speed, and lower body power [26,27]. Agility, coordination, and dynamic balance will be measured by the timed up and go test (TUG) [28].

#### Patient-reported outcome measures (PROMS)

2.11.3

Dyspnea will be evaluated using the modified Medical Research Council Dyspnea Questionnaire (mMRC) [29]. Fatigue will be determined through the Fatigue Assessment Scale (FAS) [30]. Anxiety and depression will be evaluated with the Hospital Anxiety and Depression Scale (HADS) [31].

Quality of life will be assessed with the EuroQol 5D-5L. This questionnaire contains the dimensions of mobility, self-care, usual activities, pain/discomfort, anxiety/depression, and participants also classified their perception of general health status [32].

#### Daily physical activity

2.11.4

Daily physical activity will be objectively and self-reportedly assessed. The International Physical Activity Questionnaire - Short Form (IPAQ-SF) will assess self-reported information about the weekly volume spent in vigorous, moderate, and light physical activity and the time spent sitting [33].

Additionally, participants will wear GT3X + accelerometers (ActiGraph®, LLC, Pensacola, FL, USA) along with waking hours over their right hip during 7 days at the beginning of the study, during the 2-week intervention period, and for 7 days at the follow-up assessment. Accelerometer data will be processed using ActiLife software (ActiLife®, LLC, Pensacola, FL, USA).

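### The accelerometer value labelled post-intervention is recorded during the two training weeks, so it counts the supervised sessions and is biased towards GET-G, most clearly against the control group

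*Protocol article*

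**What the plan says.** Section 2.11.4 of the protocol article gives three accelerometer wear periods: "during 7 days at the beginning of the study, during the 2-week intervention period, and for 7 days at the follow-up assessment". The device is worn "along with waking hours over their right hip". Section 2.6 agrees on when the first stretch of wear stops, since patients receive an "accelerometer to measure daily physical activity during waking hours until the completion of the prehabilitation program".

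Table 1 lists "objectively daily physical activity" as a secondary outcome and marks it at baseline, post-intervention and follow-up. The note under the table places the post-intervention assessment after the two weeks are over. Section 2.11 says the same for everything except the economic analysis: "all secondary outcomes will be assessed at baseline, post-intervention (before surgery), and follow-up (30 days after hospital discharge".

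The arms differ in what happens during those two weeks. In GET-G (section 2.5.4), "participants will walk for 20 min on a treadmill at 70% of the mean speed" reached in the 6-minute walk test during week 1, with a higher speed in week 2, and resistance work is added. Respiratory training in IMT-G and EMT-G is seated (sections 2.5.2 and 2.5.3), and EMT-G adds abdominal exercises. The control group has one education session (section 2.5.1).

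**The concern.** Secondary objective ii asks what the programmes do to daily physical activity. A reader of Table 1 will take the post-intervention value as activity once the programme is over, to be set against baseline. The wear periods do not provide that. They provide activity while the programme is being delivered, recorded through all waking hours, with the supervised sessions inside the record.

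One arm's treatment is largely walking and whole-body exercise, two arms' treatment is largely seated, and the fourth arm has no training. The prescribed treatment therefore enters the outcome to a different extent in each arm. A GET-G patient who attends every session and changes nothing else would still score higher than a control patient with the same habits. The result could be read as a behavioural effect when it shows only that the sessions took place.

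**Working it through.** **1. Which wear period can supply the post-intervention value?**

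| Source | Content |
|---|---|
| Section 2.11.4 | Wear for 7 days at the start, the 2 intervention weeks, and 7 days at follow-up |
| Section 2.6 | Wear continues in waking hours until the programme is completed |
| Table 1 and its note | Value at post-intervention, meaning after the 2 weeks |
| Section 2.11 | Post-intervention, before surgery |

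No wear period starts after the last session and ends before surgery. The 2-week intervention period is the only candidate.

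**2. Number of sessions in that period.** GET-G: 3 per week x 2 = 6. IMT-G and EMT-G: 5 per week x 2 = 10. Both agree with the totals in section 2.7 (6 and 10).

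**3. Session time in the 14 days.** Minutes = sessions x minutes per session; daily average = minutes / 14.

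| Arm | Session minutes | Per day | Treadmill walking |
|---|---|---|---|
| GET-G | 6 x 45 to 6 x 60 = 270 to 360 | 19.3 to 25.7 | 6 x 20 = 120 min, 120 / 14 = 8.6 min/day |
| EMT-G | 10 x 30 = about 300 | 21.4 | 0 |
| IMT-G | 10 x 20 = about 200 | 14.3 | 0 |
| Control | 0 | 0 | 0 |

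Section 2.5.4 states 20 min of walking for week 1 and changes only the intensity for week 2, so 20 min is assumed to hold in both weeks. Full attendance is also assumed.

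Total session time does not single out GET-G, because EMT-G's 300 min lies inside GET-G's range. What sets GET-G apart is the type of activity: the 8.6 min/day of walking.

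**4. What 8.6 min/day could do to a test against control.** The documents give no between-patient SD, so a range of 10 to 30 min/day (of walking or moderate activity) is assumed. The other inputs are 45 analysed per arm (section 2.13), two-sided 0.05, and no true change in habitual activity. With the normal approximation:

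chance of significance = Φ( 8.57 / (SD x √(2/45)) − 1.96 )

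| Assumed SD (min/day) | Standardised difference | Chance of a significant result |
|---|---|---|
| 10 | 0.86 | 0.98 |
| 15 | 0.57 | 0.77 |
| 20 | 0.43 | 0.53 |
| 25 | 0.34 | 0.37 |
| 30 | 0.29 | 0.27 |

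For SD 10: 8.57 / (10 x 0.211) = 4.07, and Φ(4.07 − 1.96) = 0.98. For SD 30: 8.57 / (30 x 0.211) = 1.36, and Φ(1.36 − 1.96) = 0.27. Over the whole range the chance is well above the nominal 0.05.

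**5. With session time removed,** the sessions contribute 0 min/day in every arm.

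**The case against.** The best defence has three parts.

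- **Filtering is data processing.** A condensed article may leave it to the full protocol or to the analysis plan, which section 2.15 promises to make available. That is fair as regards processing detail, and its absence is not the complaint. But the wear periods and the time-point label are both fixed in the article, and they conflict. No later analysis can create a wear period that was not scheduled. The only session record the article describes is attendance (section 2.7).
- **Total activity on the programme is a legitimate quantity.** It shows whether sessions add to the rest of the day or displace it. This stands, and is why total activity should still be reported. It does not justify calling the value post-intervention, or reading it alone as a change in habits.
- **Reassessment repeats the baseline procedures** (section 2.6), which might imply another 7-day wear. The explicit wear periods in sections 2.6 and 2.11.4 do not include one.

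Some stronger readings are tempting but not supported:

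- A reader might infer that GET-G *would* be shown superior to all three other arms. With no SD given, significance even against control is uncertain. Against IMT-G and EMT-G, EMT-G's session time is similar, and 10 hospital visits against 6 bring travel activity of unknown size. Part of a GET-G session is also stretching and body-weight or band work, which a hip-worn device may register weakly.
- A reader might infer that the education class contaminates the 7-day baseline wear. Section 2.5 says that, whatever the arm, "patients will start the intervention one week after the baseline evaluation". For control the class is the intervention, and section 2.6 puts the class and the start of training together. Read together, the class follows the baseline week. Every arm receives it in any case.
- A reader might extend the point to IPAQ-SF, which asks about weekly volume. Its recall week may overlap the last training week, but the gap between last session and reassessment is not given.

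**Conclusion.** The point holds for objective daily physical activity at the post-intervention time point. The value labelled that way can only come from the training weeks, and as written it includes supervised sessions. GET-G gains 8.6 min/day of prescribed treadmill walking that no other arm has. The resulting bias towards GET-G is clear against control and probable, though less certain, against IMT-G and EMT-G.

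The timing conflict rests on the text alone. The 8.6 min/day rests on full attendance and 20 min of walking in both weeks. The 0.27 to 0.98 chance of a significant difference from control rests on an assumed SD and is an illustration, not a prediction.

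The primary outcomes and the baseline and 30-day accelerometry are not affected. The correction is worth making because it is cheap and bears directly on secondary objective ii.

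**What to change.** - In section 2.11.4 and Table 1, relabel the second accelerometer measure as activity during the intervention period.
- Add session start and stop times to the attendance record the physiotherapists already keep. Recruitment began in June 2025, so this should be done promptly: times not recorded may not be recoverable.
- Make activity outside supervised sessions the between-arm comparison for daily activity, and report total activity separately. Either remove session time from the record or use non-session days only. At one session per day, the second option leaves 14 − 6 = 8 days in GET-G but 14 − 10 = 4 in IMT-G and EMT-G, so removing session time keeps more data and treats the arms more alike.
- Leave the IPAQ-SF wording unchanged, since altering it at one time point would break comparability with the other two. Note in the report that its recall week may overlap the last training week.

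The cost is two extra entries per session, one filtering step and slightly less analysable wear time. No visit or intervention changes.

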#### Economic impact

2.11.5

Specific costs are attributed to each intervention, and the cost-effectiveness of each program is compared, considering the occurrence and severity of PPC, other complications, LOS, and hospital readmissions related to surgery.

### Other outcome measures

2.12

This section outlines additional outcome measures that will be collected to provide a comprehensive understanding of the study participants and potential influences on the primary and secondary outcomes.

At baseline, participants will undergo an interview to assess their sociodemographic variables such as age (years), academic level, and civil status. The medical history, including any diagnosed diseases and the number of medications they are currently taking, will be documented by one of the research members.

Furthermore, potential barriers for the prehabilitation program will be evaluated at baseline using a questionnaire adapted from Ghisi et al. (2012) [34]. All patients who fulfill the inclusion criteria, even those who decline to participate in the clinical trial, will be asked to answer the questionnaire. This 21-item questionnaire employs a 5-point response scale for the initial 20 questions and allows for an open-ended response to the final question.

Body composition (body mass (kg), fat-free mass (kg), and fat mass (kg)) will be measured at three assessment points using bioimpedance analysis with the InBody 770® device (InBody Co. Ltd., Seoul, South Korea). Body Mass Index (BMI) will also be calculated.

Tobacco smoking habits will also be recorded at three assessment points categorized as “never smoker”, “former smoker”, or “smoker”. The tobacco consumption will be calculated by the number of pack-years using the formula: number of cigarettes per day/20 x number of smoking years [35].

Finally, food intake, including alcohol consumption, will be measured using a 1-day food record, for which participants will receive detailed instructions on accurate recording. The collected dietary data will then be analyzed using the Food Processor Software®.

